## Abstract

**Supplementary Information:**

The online version contains supplementary material available at 10.1038/s41598-026-42459-2.

## Introduction

Depression is the second most prevalent mental disorder worldwide and is associated with the highest burden of disease among all psychiatric disorders^1,2^. The lifetime-prevalence of major depressive disorder (MDD) in Germany is estimated to be 11,6%^3^. MDD is a major risk factor for suicide and is associated with higher risk for somatic diseases and mortality^4–6^ and therefore it is also a vast burden for the healthcare system^7,8^. To treat depression, pharmacotherapy and psychotherapy are the standard of care. Still, response rates are in general moderate: approximately 30% of the patients show a treatment-resistant course of disease^9^. Especially for those patients, neurostimulation treatments like repetitive transcranial magnetic stimulation (rTMS), electroconvulsive therapy (ECT) or vagus nerve stimulation (VNS) are important therapeutic strategies^10,11^.

In Europe, invasive VNS has been approved for the treatment of drug-resistant epilepsy since 1994 and for the treatment of treatment-resistant depression (TRD) since 2001^12,13^. In 2005, invasive VNS was approved by the US Food and Drug Administration (FDA) for the treatment of MDD that has not responded to at least four adequate trials of antidepressants^14^. Invasive VNS requires the surgical implantation of an impulse generator^13^. Because of the associated possible surgical complications as well as high treatment costs, invasive VNS is not often used in the treatment of depression^15^. Transcutaneous auricular VNS (tVNS), on the other hand, is a non-invasive alternative to traditional invasive VNS. During tVNS, a transcutaneous impulse generator stimulates the auricular branch of the vagus nerve (ABVN) using soft electrical currents. The direct neuroanatomical connection of the auricular branch of the vagus nerve to the nuclei of the brainstem is a possible pathway through which tVNS may exert its biological effects^16^. During the last decade, the effects of tVNS have been examined in an increasing number of clinical trials and across many different clinical populations and disorders, with depression being one of the most prominent areas of interest^17^. Studies have jointly suggested that tVNS may be an effective and well tolerated treatment for MDD^18,19^, peripartum depression^20^, and TRD^21^. Evidence for the potential of tVNS to improve MDD comes from meta-analyses, although these analyses included a relatively small number of studies, some of which exhibited methodological limitations^22,23^. Meanwhile, the safety and tolerability of tVNS is well established and it has not been associated with severe adverse effects unlike invasive VNS^15,24^. Potential side effects of tVNS are mild and local symptoms and include, but are not limited to, skin irritation along with non-specific symptoms like transient mild headache or dizziness^15,25^. Along with its tolerability, the enhanced accessibility and ease of application of tVNS, compared to other neurostimulation methods, further contribute to its feasibility^26^.

In the German, but also other national depression treatment guidelines, tVNS is still considered an experimental treatment^11^. Reasons for this categorization come from the relative novelty of the intervention, the limited high-quality evidence from randomized clinical studies, the not yet fully understood biological mechanisms of action^26^, and the limited knowledge about the optimal stimulation parameters^25,27^.

To date, numerous hypotheses have been proposed regarding the biological mechanisms underlying the antidepressant effects of invasive vagus nerve stimulation and, by extension, transcutaneous VNS. The proposed mechanisms include, but are not limited to, changes in functional brain connectivity, modulation of neurotrophins and subsequent increase of neurogenesis, inhibition of systemic inflammation, normalization of the hypothalamus-pituitary-adrenal (HPA) axis, modulation of neurotransmission, and changes in the gut microbiome^26–33^. For these hypotheses, there is only limited or indirect evidence primarily from preclinical studies or from application of VNS in other disorders^26,30^. To date, however, it is unclear which of these mechanisms contribute to the therapeutic effects of VNS in depression. It is thus not surprising that, so far, no reliable bio- or predictive markers exist for tVNS in depression^25^.

To address these issues, we developed and initiated the AddVNS study. The primary objective of the study is to identify biological, psychological, socio-demographic, and clinical biomarkers associated with augmentative tVNS in patients with a depressive episode.

## Study design

The AddVNS study is a monocentric, exploratory, prospective, randomized, double-blind, sham-controlled interventional study with a recruitment period of 3 years. It commenced in 2025 and is conducted at the research hospital of the Max Planck Institute of Psychiatry (MPIP). The study information has been aligned and filled out in the SPIRIT guidelines including a schematic participant timeline diagram (Fig. 1). Also, the research protocol version 1.0, structured in accordance with the Research Ethics Review Committee of the World Health Organization, can be found in the supplement.

**Fig. 1 Fig1:**
[figure not shown]
Schematic diagram of participant timeline in the AddVNS study. Patient health questionnaire 9 and 15 (PHQ9 and PHQ15), Beck Depression Inventory II (BDI-II), Snaith-Hamilton-Pleasure-Scale (SHAPS), Rejection Sensitivity Questionnaire (RSQ), World Health Organization Disability Assessment Schedule 2.0 (WHODAS 2.0.), Montgomery–Åsberg Depression Rating Scale (MADRS), Hamilton Rating Scale for Depression with 21 items (HAM-D21), Hamilton Rating Scale for Anxiety (HAM-A), Global Assessment of Functioning (GAF), Pulse plethysmography (PPG), Personality Inventory for DSM-5 Brief form (PDI-5), functional MRI (fMRI). Created with Biorender.com.

Participants receive either tVNS or sham tVNS for 6 weeks in addition to treatment-as-usual (TAU). Psychophysiological assessments, clinical interviews, blood draws, and stool collection are scheduled at baseline as well as 3 and 6 weeks after tVNS start. A functional MRI (fMRI) session as well as an extensive neuropsychological assessment is performed at baseline and after 6 weeks post tVNS start. Additionally, a personality self-report assessment is acquired at baseline. Furthermore, participants are asked to complete self-rating questionnaires on a weekly basis. The optional questionnaire-based follow-ups are inquired 6 and 12 weeks after tVNS end. Study duration thus amounts to 8 weeks plus 12 weeks of follow-up.

The study will start with a pilot. Here, two additional psychophysiological measurements (amounts to a total of five measurement time points) will be conducted during tVNS stimulation up to 20 participants after the initial psychophysiological assessment at baseline and following 3 weeks of tVNS application. The objective of this pilot is to examine acute effects of tVNS on psychophysiological parameters, providing first insights into the potential mechanisms of action. Owing to the exploratory and first-in-field nature of this study, patient and public involvement was not included in the study design. The AddVNS study’s multi-omics read-outs are shown in Fig. 2.

**Fig. 2 Fig2:**
[figure not shown]
Graphic summary of the AddVNS study’s multiomics approach. Created with Biorender.com.

### Participants

Only adult patients (≥ 18 years) with current MDD or bipolar disorder with current depression (BD) who are treated at the MPIP’s research hospital (either inpatient or day clinic treatment) and are able and willing to give informed consent can participate in the AddVNS study. Inclusion criteria are: (1) age 18–65 years, legally competent and able to provide informed consent; (2) diagnosis of a depressive episode (MDD or BD) according to ICD-10 or ICD-11; (3) signed informed consent documents for the AddVNS study; (4) signed informed consent and participation in the biobanking project of MPIP (Project No. 338 − 15). Exclusion criteria are: (1) age < 18 years or age > 65 years; (2) pregnancy or planning to get pregnant during the study period, breastfeeding; (3) legal supervision; (4) pervasive developmental disorders and/or intellectual disability; (5) acute substance abuse (e.g., alcohol, prescription or illicit drugs); (6) severe neurological disease; (7) anatomical or technical impossibility of tVNS administration (e.g., microtia, anotia, or history of vagotomy); (8) current treatment with an established neurostimulation method (e.g., ECT, rTMS, VNS); (9) metallic foreign bodies, implanted intracranial devices or cerebral shunts; (10) severe general illness (e.g., relevant anemia requiring transfusion, high-grade cardiac arrhythmia, severe cardiomyopathy); (11) active implants (e.g., cochlear implant, pacemaker, implantable cardioverter-defibrillator).

### Randomization and blinding

After inclusion, participants are randomized to verum or sham tVNS. Participants are blinded to their study arm, since the verum and sham electrode look alike and the weekly titration was performed in both groups. Investigators performing study assessment are also blinded to the study arm, except for study personnel responsible for the stimulation parameter settings and weekly titration. A block-wise randomization approach was chosen^34^. This design was selected to reduce the likelihood that participants in different intervention arms would share information about their stimulation-related experiences or sensations. Participants within a block receive the same intervention. Block sequence and size was based on an allocation list. A new block is started after the study participation for the patients of the previous is completed. Blinding integrity was assessed during the final week of the sham/verum tVNS by asking participants to indicate which treatment arm they believed they had been assigned to.

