### Sample size calculation

Earlier tVNS studies with a design similar to AddVNS, which have focused on clinical outcomes rather than biological ones, have shown low to moderate effect sizes^18,19,23,35^. Moreover, depression is a complex and multifactorial disease, which emerges through the long-time interaction between genetic predisposition and environmental factors^78^. Since no prior multi-omics studies on tVNS effects are available, the sample size calculation was based on the average effect sizes reported in existing clinical tVNS studies. This approach assumes that clinical efficacy reflects the aggregate downstream effects of multiple interacting biological pathways underlying tVNS and can therefore serve as a pragmatic proxy of expected average effect size of omics domains in the absence of direct multi-omics effect size estimates. Such an approach can be considered contemporary and appropriate for early-phase or exploratory multi-omics trials^52,79,80^. In addition, the AddVNS study incorporates an internal pilot phase. Should pilot data unexpectedly indicate that the main assumption regarding effect size is significantly inaccurate, sample size estimates will be updated prior to completion of recruitment, in line with established methodological recommendations^81,82^. Using a G-power calculation tool^83^, we estimated a sample size of *n* = 86 (ANOVA with repeated measures, 2 groups, effect size Cohen’s f = 0.25, significance level a = 0.05, power = 0.95, allocation in study arms 1:1, correlation between repeated measures = 0.3).

Based on prior experience with stimulation studies conducted at our clinic^52^, the AddVNS study anticipates a study discontinuation rate (including loss to follow-up) of approximately 30%. To account for this, we plan to recruit up to *n* = 112 participants, ensuring that at least *n* = 86 complete datasets are available for statistically meaningful analyses in accordance with the sample size calculation. Data from participants who discontinue the study will be included in the final analyses under an intention-to-treat framework. In addition, if more than 10% of data are missing, missing values will be handled using established imputation methods and the results will be compared with those obtained from the intention-to-treat analyses. Using heart rate variability-based stratification, among other psychophysiological and fMRI measured (e.g., pupil size), subgroup analyses will be performed.

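### Whole sequential blocks are allocated to one arm, but n = 86 and its 95% power assume independently randomised participants, and no block or period term is listed

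*Protocol article*

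**What the plan says.** The section Randomization and blinding opens at participant level: "After inclusion, participants are randomized to verum or sham tVNS". It then describes something different: "Participants within a block receive the same intervention". On timing it says "A new block is started after the study participation for the patients of the previous is completed", and on the block structure only "Block sequence and size was based on an allocation list". The stated purpose, repeated in the Discussion, is to keep participants in different arms from comparing what they feel.

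The Sample size calculation section uses "ANOVA with repeated measures, 2 groups, effect size Cohen’s f = 0.25, significance level a = 0.05, power = 0.95", with 1:1 allocation and a correlation of 0.3 between repeated measures, and arrives at n = 86. That 0.3 is a correlation within a participant, not between members of a block.

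The section Main hypotheses and statistical analyses says the focus is longitudinal change between arms. It names age, sex, socioeconomic status, BMI, smoking, pharmacological treatment and comorbidities as covariates. Neither block nor calendar period is among them.

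**The concern.** In ordinary permuted-block randomisation both arms occur inside each block, and the participant is the unit randomised. Here a block contains one arm only, so this is a cluster design with sequential clusters. Anything that varies over calendar time and affects change over the six weeks (season, staffing, usual-care practice, scanner drift) falls wholly on one arm within a block. It averages out between arms only over the number of blocks, not over the number of participants.

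If outcomes within a block are positively correlated, an analysis that treats participants as independent has standard errors that are too small, and a period effect can be reported as a biological effect of tVNS. Identifying such effects is the trial's main objective. The stated power is also too favourable for the design described.

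**Working it through.** **1. The stated figure.** The article does not give the number of measurements or which ANOVA effect was tested. One set of inputs that returns 86 is the between-factors test with m = 7 (weekly values, weeks 0 to 6):

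λ = f²·N·m / (1 + (m − 1)ρ) = 0.0625 × 86 × 7 / (1 + 6 × 0.3) = 37.625 / 2.8 = 13.44, on 1 and 84 df, power 0.952.

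Other choices give other sizes: between-factors needs 114 with m = 3 and 138 with m = 2; the within-between interaction needs 60 and 76. None of them contains an allowance for blocks.

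**2. How many blocks can there be?** Recruitment lasts 3 years, about 156 weeks (Study design). Participation is 8 weeks plus 12 weeks of follow-up. Only the start of a block has to fall inside the recruitment period.
- 8 weeks per block: starts at weeks 0, 8, …, 152, so at most 20 blocks.
- 20 weeks per block, if follow-up counts as participation: starts at weeks 0, 20, …, 140, so at most 8 blocks.

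Both limits assume that each block fills at once; staggered entry lowers them. Two illustrations for about 86 completers are 18 blocks of 5 (86/18 ≈ 4.8) and 8 blocks of 11 (86/8 ≈ 10.8).

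**3. Formulas.** K is the number of blocks and b the block size. The ICC is assumed to be 0.01 to 0.10, and means the ICC of the change being analysed.
- Design effect: DE = 1 + (b − 1)·ICC.
- Type I error when blocks are ignored: 2·(1 − Φ(1.96/√DE)).
- Block-level power: two-sided t test on K − 2 df with non-centrality 3.647/√DE. The value 3.647 gives exactly 95% power on 84 df. It is held fixed although the illustrations contain 90 and 88 participants.

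**4. Results.**

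| Blocks × size | ICC | DE | Type I error, blocks ignored | Non-centrality | Block-level df | Block-level power |
|---|---|---|---|---|---|---|
| 18 × 5 | 0.01 | 1.04 | 5.5% | 3.58 | 16 | 91.8% |
| 18 × 5 | 0.05 | 1.20 | 7.4% | 3.33 | 16 | 87.8% |
| 18 × 5 | 0.10 | 1.40 | 9.8% | 3.08 | 16 | 82.5% |
| 8 × 11 | 0.01 | 1.10 | 6.2% | 3.48 | 6 | 82.4% |
| 8 × 11 | 0.05 | 1.50 | 11.0% | 2.98 | 6 | 70.0% |
| 8 × 11 | 0.10 | 2.00 | 16.6% | 2.58 | 6 | 57.9% |

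Simulating the participant-level t test with whole blocks in one arm (40,000 runs per setting) gave type I errors within 0.3 percentage points of the table.

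**The case against.** The strongest reply is that the article never gives the between-arm model. The ANOVA is a sizing device, the covariate list is at participant level, and a block random effect could stand in an analysis plan or in the supplementary protocol, neither of which is shown. That stands. A reader might infer that the analysis is known to ignore blocks; the document supports only that the sample size does, and that no block or period term is listed.

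A reader might also infer that type I error is certainly inflated. It is inflated only if the ICC is positive and blocks are ignored. The focus is on change, so stable differences in level between blocks cancel. The trial is at one centre, and some shared conditions may be common to all blocks. With small blocks and an ICC near 0.01 the inflation is slight, about 5.5%.

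Nor should the block-level loss be read as the trial's only valid power. With 8 blocks and an ICC of 0, a block-level test has 86% power, but the participant-level test would then be valid at 95%. The 86% is the price of protecting against an unknown ICC.

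A further tempting inference is that allocation is not concealed, because unblinded stimulation staff know the open block's arm. That would matter only if those staff also recruit or judge eligibility. The article does not say they do; it has a trained study physician obtain consent. It is not part of this point.

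Finally, the trial is declared exploratory, and whole-block allocation was chosen to protect blinding. Both are fair, but neither makes a calculation for independent participants match the design.

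**Conclusion.** The point holds for the sample size as written: the stated 95% power ignores the unit randomised. For the analysis it holds conditionally, because the full model is not shown.

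The direction is certain for any positive ICC; the size is not. It rests on an assumed ICC of 0.01 to 0.10 and on block numbers that the article leaves to the allocation list. If follow-up counts as participation, 8 blocks is the upper limit rather than a pessimistic case, and the few block-level degrees of freedom become the larger part of the problem at low ICC. It should be corrected before any between-arm analysis is run.

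**What to change.** 1. **Analysis.** For every between-arm comparison, fit block as a random effect, with participant nested in block, and use Satterthwaite or Kenward-Roger degrees of freedom. Block cannot be a fixed effect, because arm is constant within a block and would be absorbed.
2. **Check.** Permute arm labels over whole blocks only as a sensitivity check, and only if there are enough blocks. With 6 blocks (3 v 3) there are 20 allocations, so the smallest two-sided p is 2/20 = 0.10.
3. **Power.** State the number and size of blocks from the allocation list, say whether follow-up must end before the next block opens, and restate the power of n = 86 over an ICC range.
4. **Wording.** Say plainly that blocks, not individual participants, are randomised.

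Cost: text changes, wider intervals and a less favourable stated power. No new patients or procedures are needed for this. Restoring 95% would need more completers: 86 × DE gives 90 to 121 for blocks of 5 (86 × 1.04 to 86 × 1.40) and 95 to 172 for blocks of 11 (86 × 1.10 to 86 × 2.00), before the further loss from few blocks. The sponsor may reasonably accept the lower power in an exploratory trial, provided it is stated.

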### Intervention

Participants receive either tVNS or sham tVNS for a period of 6 weeks. Both interventions are administered as an adjunct to TAU, which is provided by the participants’ attending physicians and psychologists according to clinical expertise and guidelines. Both tVNS and sham tVNS intervention are carried out three times a day (morning, noon, evening) from Monday to Friday. Each of the three daily stimulation sessions lasts 30 to 60 min, depending on the individual tolerance (= individual subjective comfort and tolerability of stimulation) of the participant. Flexibility in stimulation duration was permitted to optimize adherence by accommodating individual tolerability, preferences, perceived autonomy, and comfort.

The stimulation is performed with the device tVNS E ^®^ (tVNS Technologies GmbH, Erlangen, Germany). The device is CE certificated and approved as Class IIa medical device under the Medical Device Regulation of the European Union. The device consists of a stimulator the size of a small cell phone and an ear electrode that is placed at the stimulation site.

The stimulation protocol was developed considering earlier tVNS studies and the mandatory sections of the device’s instruction manual^20,21,35^. The stimulation site is the cymba concha of the left ear, since the latter is thought to be exclusively innervated by the vagus nerve^36^. Thus, the left vagus nerve is stimulated (similar to invasive VNS), which is thought to reduce the risk of bradycardia since the right vagus primarily innervates the sinoatrial node of the heart, although human studies are still needed to confirm this distinction and its clinical relevance^37^. Nonetheless, right-sided or even bilateral tVNS has been shown to be safe^15^. Prior to the actual stimulation, stimulation intensity (electrical current) is determined by titration. Here, the highest level (mA) tolerated by the patient, that is the value between the individual perception- and pain threshold, is used for the longitudinal tVNS stimulation. During weekly titration sessions, stimulation intensity was adjusted beginning at the lowest level (0.1 mA) and increased in 0.1 mA increments until a clearly perceptible yet comfortable sensation was achieved, without pain, up to a maximum of 5 mA. Electrical current of the tVNS E ^®^ can be adjusted between 0.1 and 5.0 mA. Other stimulation parameters are set to the device’s default settings: biphasic stimulation, frequency 25 Hz, pulse-pause ratio 28 s : 32 s.

During the first tVNS stimulation session, study personnel provide detailed instructions on how to use the device in person. In the following sessions, participants perform the thrice daily stimulations by themselves and can reach out to study personnel if questions arise. Any adjustments to the current intensity, including titration during the intervention period, are performed by study personnel only. If a participant intentionally alters stimulation parameters including localization of the ear-electrode in a way that endangers either blinding or the study objective, the individual will be excluded from the study. In addition, regular check-ups are performed by study personnel to prevent errors during the stimulation.

Sham tVNS is performed identical to tVNS, with the only exception that the sham tVNS is conducted with no current using the manufacturer’s tVNS E ^®^ sham electrode. Visually, the sham electrode cannot be distinguished from a regular stimulation electrode. This approach was chosen to maximize discrimination between specific neurostimulatory effects and non-specific contextual or placebo effects, while still matching key elements of intervention.

The time and duration of each stimulation session is documented by the patient. Additionally, the app (*tVNS® Patient*) is used to retrieve, track, and double-check stimulation parameters. This systematic documentation enables dose–response analyses. To prevent unblinding, only investigators responsible for stimulation have access to the app.

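### Participants who tamper with stimulation are excluded from the study after randomisation, and this rule is not reconciled with the promised intention-to-treat analysis

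*Protocol article*

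**What the plan says.** All references are to the protocol article.

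- **Randomization and blinding:** "After inclusion, participants are randomized to verum or sham tVNS". Outcome assessors are blinded. The staff who set and titrate the stimulation are not.
- **Intervention:** if a participant intentionally alters stimulation parameters, electrode position included, "in a way that endangers either blinding or the study objective, the individual will be excluded from the study". The section does not say who decides this, whether assessments stop, or what happens to data already collected. It also says that the app used to check stimulation parameters is open only to the investigators responsible for stimulation.
- **Sample size calculation:** "Data from participants who discontinue the study will be included in the final analyses under an intention-to-treat framework". On missing data: "if more than 10% of data are missing, missing values will be handled using established imputation methods", after which "the results will be compared with those obtained from the intention-to-treat analyses".
- **Study design, MRI scans, Psychophysiological assessment:** MRI is acquired at baseline and after 6 weeks only. Psychophysiology is measured at baseline, week 3 and week 6.
- **Study objectives:** the main objective is to identify neuroimaging and psychophysiological changes associated with tVNS.

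**The concern.** An intention-to-treat comparison is protected by randomisation only while people are not removed for what they do after allocation. The exclusion rule removes them for exactly that. One section speaks of exclusion and the other of discontinuation, and nothing links the two.

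Three features make this more than a matter of wording.

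1. **The criterion is a judgement.** Whether an alteration endangers the study objective is open to interpretation.
2. **Knowledge of the arm can enter.** Parameter changes would show up in the app, which only unblinded stimulation staff can open.
3. **The behaviour may depend on the arm.** Verum current is raised until it is plainly felt, and sham delivers none. Verum participants might move the electrode or try to reduce the sensation. Sham participants might interfere because they feel nothing.

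A further problem arises at data collection. A person excluded between baseline and week 6 has no second scan and so no observed imaging change. No later analysis plan can restore an assessment that was never made.

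The missing-data rule adds to this. Imputation is set beside the intention-to-treat analysis rather than inside it, and it is triggered by the amount missing, not by whether the loss differs between arms.

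**Working it through.** **Reading the sections together**

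| Step | Section | What follows |
|---|---|---|
| Allocation | Randomization and blinding | Takes place after inclusion, before stimulation |
| Exclusion for altering stimulation | Intervention | Necessarily after allocation; status of data not stated |
| Intention-to-treat | Sample size calculation | Covers those who discontinue; excluded participants not mentioned |
| MRI | MRI scans | Two time points; exclusion before week 6 leaves baseline only |
| Psychophysiology | Psychophysiological assessment | Exclusion before week 3 leaves baseline only; between weeks 3 and 6, no end-of-treatment value |

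On the narrow reading, an excluded participant's data are removed, which contradicts intention-to-treat. On the generous reading, earlier data are kept, but the participant still has no observed imaging change.

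**The plan's own figure, used only as a yardstick**

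The article gives no exclusion rate. Its effect size comes from the sizing calculation: "ANOVA with repeated measures, 2 groups, effect size Cohen’s f = 0.25". The other stated inputs are ρ = 0.3 for repeated measurements, equal arms, 95% power and a 5% level. The number of measurements m is not stated. For the between-groups test, λ = f²·N·m / (1 + (m − 1)ρ). With N = 86 and m = 7 (assumed):

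- λ = 0.0625 × 86 × 7 / (1 + 6 × 0.3) = 37.625 / 2.8 = 13.44
- F test with 1 and 84 degrees of freedom: power 0.952

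So the stated 86 reproduces under that reading. For two equal groups, f = 0.25 then corresponds to a difference of 2 × 0.25 = 0.5 SD between arms.

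**Possible shift from exclusions in one arm (assumed inputs)**

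Let a share e of one arm be removed, and let those removed differ by d SD from those kept. The full-arm mean equals the kept mean plus e·d, so the shift is e × d.

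| e | d = 0.25 SD | d = 0.5 SD | d = 1 SD |
|---|---|---|---|
| 5% | 0.0125 | 0.025 | 0.05 |
| 10% | 0.025 | 0.05 | 0.10 |

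Against 0.5 SD, this runs from 0.0125/0.5 = 2.5% to 0.10/0.5 = 20% of the planned effect.

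**The 10% trigger**

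With 1:1 allocation, losing 10% of one arm and none of the other is a loss of 5% overall. A purely one-sided loss of the size in the table would therefore not, on its own, reach the trigger. With the expected discontinuation of about 30%, the trigger would probably be reached for end-of-treatment readouts, but for reasons unrelated to this imbalance.

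**The case against.** The case against is substantial, and part of it stands.

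- **The sections can be read as compatible.** Exclusion appears under Intervention and mentions neither analysis sets nor deletion of data. Someone excluded can be read as a participant who discontinued, whose data are kept. This stands as a possible reading, so it cannot be said that the analysis set *is* selected after allocation, only that it may be. It does not answer the missing week 6 assessments.
- **The event may be rare.** The rule requires intent and a threat to blinding or to the objective. Only staff adjust the current, check-ups are regular, and session length already bends to tolerance. This stands, and it is why the size is left open.
- **Analysis sets and missing-data methods are commonly left to a full protocol or analysis plan, which is not shown.** True of what is absent. The exclusion rule and the 10% trigger, however, are stated in the article.
- **Comparing imputed with intention-to-treat results may be an ordinary sensitivity comparison.** Possible. The wording still leaves open how intention-to-treat includes people without outcomes.

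A reader might go further and infer that repeated-measures ANOVA discards incomplete cases, so that at 30% loss only 112 × 0.70 = 78.4, about 78, are analysed and 34 of 112 are left out. The article does not support this. ANOVA appears only as a sizing input, the analysis section names no model for the arm comparison, no text says incomplete cases are dropped, and imputation would probably apply at that level of loss. The 30% also includes loss to follow-up, which need not all fall before week 6. Nor does the article say that readouts with 10% or less missing revert to complete cases. It simply states no handling for them.

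**Conclusion.** The point holds as an unreconciled conflict with a plausible route to bias. A discretionary exclusion after randomisation sits beside an intention-to-treat promise, the relevant app evidence is visible only to staff who know the arm, and following the rule literally removes the end-of-treatment measurements that the main objective needs. That exclusions would differ by arm is plausible but not shown.

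The size is unknown. The 0.01–0.10 SD range rests on an assumed 5–10% removed from one arm only and an assumed difference of 0.25–1 SD. Its upper end is a fifth of the 0.5 SD yardstick, and the rest is smaller. This is modest, but it is avoidable and should be corrected.

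**What to change.** 1. **Reconcile the Intervention and Sample size calculation sections.** State that participants who meet the alteration criterion are recorded as protocol deviations, are invited to the remaining scheduled assessments, stay in the intention-to-treat set with all observed data, and are left out only of a per-protocol sensitivity analysis. Whether stimulation continues is a separate matter for the investigators.
2. **Place missing-data handling inside the intention-to-treat analysis.** One option is a likelihood-based mixed model on all observed visits of all randomised participants. Run imputation as a sensitivity analysis whatever the percentage missing, instead of only above 10%.

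**Cost.** More than wording: some added visits, including MRI, for the few participants concerned, and an amendment that the Ethics section requires to be reviewed before implementation. Keeping these participants will dilute the estimated effect slightly. Since the study began in 2025, the change is worth making early, because assessments missed in the meantime cannot be recovered.
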